### Study procedures

#### Testing locations

Participants will be recruited from Broward and Palm Beach Counties in Southeast Florida. Florida Atlantic University (FAU) has several campuses in Broward and Palm Beach Counties. FAU’s Memory and Wellness Center is on the main Boca Raton campus and will serve as a testing and sensor installation/maintenance site as will the Clinical Research Unit, also on the main campus. Secondary sites will be on the Davie campus in central Broward, and several cooperating places of worship and community centers for the convenience of those older drivers who customarily drive within a restricted range. A subaward to colleagues in Psychology, Engineering, and Nursing at the University of Central Florida (UCF) will support the recruitment and testing of eligible participants on the UCF campus in Orlando, Florida. Data will be transmitted securely to FAU for analysis.

#### Enrollment procedures

Older drivers who express an interest in participation will receive an explanation of the study and the activities that participation entails. They will then be screened for eligibility and proceed to the first set of assessments. An installation team will place the telematics and video sensors in participants’ vehicles while the cognitive tests are administered.

#### Scheduling over 3 years

The project aims to identify cognitive changes over time that may be associated with indicators from the in-vehicle sensors. Therefore, cognitive assessments are administered every 3, 6, and 12 months (depending on the tests) for 3 years, for a total of 13 quarterly assessments. Every 3 months the following cognitive assessments will be administered: MoCA, FAQ, GDS-15, and the DSAQ (Driver Sensor Acceptability Survey which responds to Aim 3 of the study (See list of abbreviations)). The IDN, GMLT, ONB, and TWOB will be administered at every time point except for Visit 1 in order to keep the first visit under 3 h. Since we will use parallel forms of these tests, they do not need a double baseline. The following assessment tools will be administered beginning with Visit 2 and again on Visit 3 for the double baseline, then every 6 months: ECog, BFD, TMT, AFT, SCWT, VF, and MINT. The UFOV will be administered on Visits 1 and 2, then repeated every 6 months. Lastly, the LASSI-L and Craft Story will be administered at visits 1 and 2 for the double baseline and then every 12 months. The MMSE will be administered on visits 1, 5, 9, and 13.

### Preparation of assessors and psychometricians

Experienced nursing and psychology students and postdoctoral fellows will perform the clinical and cognitive assessments. These research assistants will go through intensive training in the administration and scoring of the assessments. They are first exposed to these procedures via training videos followed by one-to-one observation sessions with clinicians and experienced psychometricians who explain the administration and scoring procedures for each assessment measure in detail. After training, each research assistant will submit videos of themselves performing the clinical and psychometric assessments with non-participant volunteers. Individual feedback is provided regarding any deviations from the standard administration, and if necessary, a second video is requested. Approval to conduct assessments independently is obtained after completing an additional 4–6 shadowing sessions, during which the newly trained research assistants will be observed administering the assessments.

The clinical diagnosis will be made by a team of neurologists, neuropsychologists, and geriatric nurses who review the clinical and psychometric data using the Algorithmic Diagnosis procedure described above. Clinical personnel are blinded to the data driving the decision in order to avoid potential bias in the diagnosis.

#### Controlling for practice effects

Important issues in this study of cognitive change are the potential for practice and retest effects in performance on repeatedly administered cognitive tests, a problem common to longitudinal studies. Although we may assume that these effects are observed in all clinical groups, they may not be equivalent across groups.

While there is no clear consensus on the best methods to address this problem, we will address it by:Using alternative forms with equivalent psychometric properties where available. The IDN, ONB, TWOB, and the GMLT are short and repeatable assessments that are unaffected by language, therefore we are able to have a large stimulus set that is controlled and randomized so that each participant has a unique stimulus set at each time point. The AFT uses a set of pseudo randomizations controlling for the number of congruent and incongruent trials.The most prominent practice effects generally take place between the first and the second administration of a test. For this reason, we will use a double baseline design in which the second assessment (3 months after the first) will be used as the baseline for all cognitive measures.In the statistical analysis we will include reliable change indices (RCIs), and regression base analyses with correction for practice effects.

### Statistical analysis

#### Data processing phase

Data processing will occur in three steps. First, several preliminary models will be created to provide greater flexibility in analyzing the relationships between the driving behaviors and cognition over time. Various models such as linear mixed models and non-linear functions, such as splines, will be assessed.

The second processing step is feature extraction. Variables will be created from the raw data, with mean, standard deviation, and assessment of normality analyzed. During this step the telematic and video data will be standardized so that all of the features will account for driving speed and length of time driving during each trip. Since the telematic and video data have varying scales, data will be normalized using the minmax approach. Lastly, external weather and traffic conditions data will be added to the database.

The third processing step is the reduction of the number of features to prevent overfitting the model as well as to reduce the complexity of the model. Two strategies will be used to complete the feature selection step. Elastic net regression adds a penalty and bias to the models resulting in the retention of only the critical variables. These results will be compared to the results for the second method, SHAP (Shapley Additive exPlanations) analysis, which is a global feature selection method that will be used to compute the feature importance of each variable in predicting cognitive change [45].

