The telematics sensor employs hybrid data logging systems: onboard and cloud data logging. High-resolution telematics data will be stored in local (in vehicle) data stores, manually collected and uploaded to a secure central database during participants’ quarterly visits. The in-vehicle sensor has cellular connectivity. The Cloud database will be used primarily to check the operating state of in-vehicle sensors (e.g., error messages, local data connectivity, operating condition of camera units through Wi-Fi connections), software updates through 4G connections (e.g., change sampling rates, update OBD parameters, firmware update), and troubleshoot malfunctioning devices (e.g., remote control through 4G connections). See Fig. 1.

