#### Predictive modeling phase

Two different methods will be used to model the prediction of changes in cognitive functioning followed by a sensitivity analysis. First, a traditional predictive modeling method using a linear mixed effects (LME) model with time varying covariates will be conducted [46]. This LME method will use the processed data aggregated at weekly, monthly, and 3-month intervals along with the features determined by the SHAP analysis. The second method will use a machine learning recurrent neural network (RNN) approach to loop over and pass information from one step to another in the network allowing for the capability to effectively incorporate temporal (time) dependencies in longitudinal data [47]. With RNN, data contains data sequences from k time steps at each time point (ti), input features (Xti), and internal state (memory) from the previous time step (ht(i−1)) allowing for RNN to identify patterns hidden in the sequence of the data not detectible by conventional neural networks [48]. The Driving Behavior Indices (DBIs) algorithms generated will be assessed for ability to predict changes in overall cognitive functioning as well as other specific domains.

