#### Driving behavior (normalized driver behavior indices)

Driver Behavior Indices (DBIs) will be estimated from the telematics and vision sensor data. The selection of the DBIs is designed to reflect older drivers’ cognitive function and driving performance. To account for the variation in participants’ driving frequency and mileage, the DBIs will be normalized by the total number of trips, left turns, traveled intersections and/or total mileages. The DBIs will be evaluated for each driver and will be summarized on a daily, weekly, and monthly basis. DBIs are classified into four categories. Examples of DBIs are shown in Table 4.

**Table 4 Tab4:** Driver behavior indices

**Categories**	**DBIs**	**Data Analytics**
**Travel Patterns**	number of trips, miles driven, miles on the highway, miles during the night, daytime, and severe weather, highway miles, etc.	map-matching, data queries, map data, weather data
**Abnormal Driving**	wayfinding, getting lost, ignoring traffic signals and signs, near-collision events, distraction, drowsiness, etc.	machine vision, shortest path, outlier detection, trajectory clustering, frequent graph mining
**Reaction time**	reaction time to traffic light change, front-vehicle taillight, pothole, etc.	vision sensing, data fusion, vibration analysis, machine learning
**Braking Patterns**	eye movements and IMU data at stop signs, traffic signals, tail lights, losing focus, potholes, etc.	signal processing, gaze estimation, data mining, machine vision

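### An elastic net run on min-max-scaled features lets distribution shape affect selection: at equal association with cognitive change, skewed event indices are disfavoured and bounded indices favoured

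*Protocol article*

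**What the plan says.** The protocol article, Statistical analysis, Data processing phase, fixes an order of work. In the second step features are extracted and "Since the telematic and video data have varying scales, data will be normalized using the minmax approach". Then comes selection: "The third processing step is the reduction of the number of features to prevent overfitting the model". Two selectors are named. For the first, "Elastic net regression adds a penalty and bias to the models resulting in the retention of only the critical variables". For the second, "These results will be compared to the results for the second method, SHAP (Shapley Additive exPlanations) analysis, which is a global feature selection method".

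The second step also says that the data are "standardized so that all of the features will account for driving speed and length of time driving during each trip". That is an adjustment for exposure and does not bring features to unit variance. Means, SDs and normality are to be examined, but no transformation or other action is attached to the result. Weather and traffic data join the database after the min-max step.

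The Predictive modeling phase feeds the linear mixed effects (LME) model with processed data "along with the features determined by the SHAP analysis". Table 4 lists among the abnormal-driving indices "wayfinding, getting lost, ignoring traffic signals and signs, near-collision events, distraction, drowsiness, etc".

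**The concern.** An elastic net penalises the size of each coefficient, and that size depends on the units of the feature. Min-max scaling gives every feature the same range but not the same spread. An index with most values near zero and a long right tail keeps a small SD after scaling. It then needs a larger coefficient to express the same effect, and so pays a larger penalty. An index that fills its range, such as a share of miles on highways, pays less.

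At stake is the elastic net's list of critical variables and the planned comparison with SHAP. A difference between the two lists could come from scaling and be read as disagreement about which driving behaviours matter. Rare events such as getting lost are likely to be skewed, and the study looks for subtle change, where effects are weak and this bias is largest.

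**Working it through.** The plan gives no figure for this point, so there is none to reproduce.

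**Inputs from the article.** Min-max scaling before the elastic net (Data processing phase); 384 and 460 participants (Sample size calculation).

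**Assumed inputs.** One record per driver and 20 independent features: 10 uniform (bounded) and 10 skewed (lognormal or negative binomial). Three of each kind are truly linked to the outcome with equal standardised effects. L1 share a = 0.5, 5-fold cross-validation, penalty chosen at the minimum error (min) or by the one-standard-error rule (1SE), 60 replicates per setting.

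**Step 1, entry condition.** With the other coefficients at zero, a feature enters when |cov(x, y)| > λa, that is, |r| × SD(x) × SD(y) > λa. Min-max scaling leaves r unchanged and turns SD(x) into SD/range. Entry then depends on |r| × SD/range. After unit-variance scaling it depends on |r| alone.

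**Step 2, size of the handicap.** For a uniform feature SD/range = 1/√12 = 0.289; the simulated value was 0.29. For the skewed features it was 0.083 to 0.165. The correlation that a skewed feature needs, relative to a uniform one, is between 0.290/0.165 = 1.8 and 0.289/0.083 = 3.5 times as large.

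**Step 3, retention of truly informative features, effect 0.12 SD (bounded vs skewed).**

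| n, rule | Skewed shape | Min-max | Unit variance |
|---|---|---|---|
| 460, 1SE | lognormal | 0.38 vs 0.06 | 0.29 vs 0.32 |
| 460, 1SE | negative binomial | 0.37 vs 0.09 | 0.36 vs 0.33 |
| 384, 1SE | lognormal | 0.31 vs 0.06 | 0.31 vs 0.31 |
| 384, 1SE | negative binomial | 0.38 vs 0.15 | 0.24 vs 0.25 |
| 460, min | lognormal | 0.98 vs 0.94 | 0.96 vs 0.96 |
| 460, min | negative binomial | 0.99 vs 0.86 | 0.99 vs 0.96 |
| 384, min | lognormal | 0.95 vs 0.71 | 0.89 vs 0.89 |
| 384, min | negative binomial | 0.95 vs 0.81 | 0.96 vs 0.93 |

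Each proportion rests on 60 × 3 = 180 feature-runs. Treating these as independent, the Monte Carlo standard error is about √(0.38 × 0.62/180) = 0.04 at 0.38 and √(0.06 × 0.94/180) = 0.02 at 0.06. The 1SE gaps under min-max are far outside this error; the differences under unit variance are not.

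**Step 4, stronger effect, 0.20 SD, min-max.** At n = 460: 1.00 vs 0.96 and 0.99 (1SE), and 1.00 vs 1.00 (min). At n = 384 with 1SE: 0.99 vs 0.90 and 0.91. These runs also used less skewed features (scaled SD at n = 460 of 0.105 and 0.139, against 0.083 and 0.110 in Step 3), so the narrowing cannot be put down to effect size alone.

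**Step 5, irrelevant features.** At n = 460 with the minimum-error penalty, over both effect sizes, min-max kept irrelevant bounded features in 0.74–0.91 of cases and irrelevant skewed ones in 0.42–0.75. Unit-variance scaling gave 0.42–0.53 and 0.43–0.55. The preference for bounded features therefore persists among irrelevant ones even where the gap among informative features has closed.

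**The case against.** **The elastic net does not govern the main model.** A reader might infer that this step decides which indices reach the prediction models. The text does not support that: the LME model takes its features from SHAP, and the recurrent network's inputs are not tied to either selector. If SHAP explains a tree model, min-max scaling has essentially no effect on it; if it explains the penalised model, the bias carries over. The model is not named. This objection stands and limits the reach of the point.

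**The software may undo the scaling.** If the elastic net routine standardises internally, the effect disappears. A condensed article may leave this to the full plan. This stands as a condition. But the article does fix min-max for the features and names no other scaling before the penalised step.

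**Skewness is assumed.** No distribution is given for any index. Indices are to be expressed per trip, left turn, intersection or mile, so some event indices could themselves be bounded proportions. This stands for the size of the effect, not for its mechanism.

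**Faulty records.** A reader might infer that one corrupted sensor value will squeeze a whole feature. The Telematic units section describes cloud monitoring used to "troubleshoot malfunctioning devices (e.g., remote control through 4G connections". That shows malfunctions are anticipated and looked for; it does not show that corrupted values reach analysis. The bias needs no corrupted value.

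**Later quarters.** A reader might also infer that each new extreme rescales earlier data. Nothing says that the scaling is refitted each quarter; a single scaling of the assembled data fits the text equally well.

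**Conclusion.** The point holds in a limited form. As written, the elastic net works on min-max-scaled telematic and video features, so its effective penalty depends on SD/range. At equal association with cognitive change, skewed event-type indices are disfavoured and bounded ones favoured. In the simulations a skewed index needed about 1.8 to 3.5 times the correlation to enter. Under weak effects and a strict penalty at n = 460, retention was 0.37–0.38 for bounded against 0.06–0.09 for skewed informative features; unit-variance scaling removed the gap.

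It would be too strong to say that skewed indices are dropped whatever their link with cognition. Association still drives selection, and in the 0.20 SD runs at n = 460 the gap among informative features nearly closed. The harm is to the elastic net's list of critical variables and to its comparison with SHAP.

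The sizes rest on the assumed distributions, effects and independent features, and on software that does not re-standardise. The direction follows from the algebra, given skewness and no internal re-standardisation.

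**What to change.** For the elastic net step, replace min-max scaling with centring and division by the SD.

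- Estimate the means and SDs in training data only.
- Apply the same scaling to every candidate feature, including weather and traffic variables if they enter the selection.
- Before scaling, apply a transform that tolerates zeros, such as log(1 + x) or the square root, to skewed event rates. Because log(1 + x) is nearly linear for rates far below 1, state the unit of each rate with the transform.
- Keep min-max only where the recurrent network needs inputs between 0 and 1.

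Do not winsorise zero-heavy event indices at the 99th percentile: an index that is non-zero in fewer than 1% of records would become constant and be lost. Do not clip later quarters at baseline limits, because that would cut off the within-driver increases that the study is looking for.

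The cost is a sentence in the analysis plan and a few lines of code. The downside is that two scalings of the same features must be kept and documented.

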#### Predictive modeling phase

Two different methods will be used to model the prediction of changes in cognitive functioning followed by a sensitivity analysis. First, a traditional predictive modeling method using a linear mixed effects (LME) model with time varying covariates will be conducted [46]. This LME method will use the processed data aggregated at weekly, monthly, and 3-month intervals along with the features determined by the SHAP analysis. The second method will use a machine learning recurrent neural network (RNN) approach to loop over and pass information from one step to another in the network allowing for the capability to effectively incorporate temporal (time) dependencies in longitudinal data [47]. With RNN, data contains data sequences from k time steps at each time point (ti), input features (Xti), and internal state (memory) from the previous time step (ht(i−1)) allowing for RNN to identify patterns hidden in the sequence of the data not detectible by conventional neural networks [48]. The Driving Behavior Indices (DBIs) algorithms generated will be assessed for ability to predict changes in overall cognitive functioning as well as other specific domains.

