## Methods/design

### Objective

The objective of this study is to test an unobtrusive multi-sensor system’s ability to detect cognitive change in older (≥ 65) drivers.

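### With one coefficient per driving index, the LME mixes differences between drivers with change within a driver; a claim of detecting change needs the two separated and the outcome stated

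*Protocol article*

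**What the plan says.** All references are to the protocol article.

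- **Objective:** to test the sensor system's "ability to detect cognitive change in older" drivers.
- **Predictive modeling phase, target:** "Two different methods will be used to model the prediction of changes in cognitive functioning followed by a sensitivity analysis". The first method is the model in question: "a linear mixed effects (LME) model with time varying covariates will be conducted". Its inputs are the "processed data aggregated at weekly, monthly, and 3-month intervals along with the features determined by the SHAP analysis".
- **Data processing phase:** features are adjusted for speed and time driven, and then "data will be normalized using the minmax approach". The section does not say whether the minimum and maximum are taken over all drivers or for each driver.
- **Driving behavior (normalized driver behavior indices):** "the DBIs will be normalized by the total number of trips, left turns, traveled intersections and/or total mileages". This is a rate per unit of exposure, not a comparison with the driver's own past.
- **Controlling for practice effects:** the second assessment serves as cognitive baseline, and "we will include reliable change indices (RCIs), and regression base analyses with correction for practice effects". Neither is tied to the LME.

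The article does not state whether the LME outcome is the cognitive score at each visit, change from baseline, or a reliable change index. It also does not state whether a DBI enters as one term or as separate between-driver and within-driver terms.

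**The concern.** A time-varying DBI carries two kinds of information: how this driver differs from other drivers, and how this driver now differs from his or her usual self. Only the second answers the objective. One coefficient on the uncentred DBI is a weighted average of the two slopes. Someone who has always driven little and always scored lower can contribute to it without changing at all.

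This matters because the article wants to go beyond comparisons between groups of drivers. The Background notes that an earlier longitudinal naturalistic study could not locate the point of conversion, and hopes that this study can help to do so. The rationale under Braking patterns is also a within-driver one: drivers whose cognition changes would react differently from before. A mixed coefficient cannot show that by itself.

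**Working it through.** The article gives no figure for the LME, so there is none to reproduce.

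**Inputs from Sample size calculation:** n = 384 drivers (before the attrition allowance), T = 12 repeated measures, correlation between cognitive measures ρy = 0.5, alpha 0.05.

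**Assumed, since the article gives none:** DBI intraclass correlation ρx = 0.5 to 0.9; correlation between a driver's usual driving and usual cognition r = 0.2 to 0.3; true within-driver slope zero; unit variances.

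**Case 1: outcome is cognition at each visit.** In a random-intercept model:

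- ψ = (1−ρy)/[(1−ρy) + Tρy] = 0.5/6.5 = 0.0769
- between-driver information S_B = Tρx + 1 − ρx; within-driver information S_W = (T−1)(1−ρx)
- weight on the between-driver slope w = ψS_B/(S_W + ψS_B)
- between-driver slope β_B = r√(ρxρy)/[ρx + (1−ρx)/T]
- expected coefficient b = wβ_B; SE = √{(1−ρy)/[n(S_W + ψS_B)]}; z = b/SE
- rejection rate = Φ(z − 1.96) + Φ(−z − 1.96)

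For ρx = 0.7 and r = 0.3: S_B = 8.4 + 0.3 = 8.7; S_W = 11 × 0.3 = 3.3; w = 0.669/3.969 = 0.169; β_B = 0.3 × √0.35/0.725 = 0.245; b = 0.0413; SE = √[0.5/(384 × 3.969)] = 0.0181; z = 2.28; rejection 63%.

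| DBI ICC | weight on between-driver slope | rejection, r = 0.2 | rejection, r = 0.3 |
|---|---|---|---|
| 0.5 | 8% | 18% | 35% |
| 0.7 | 17% | 33% | 63% |
| 0.9 | 43% | 69% | 96% |

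Simulation of the same settings gave 17% to 96% for the uncentred DBI. With driver mean and deviation entered separately, the deviation term rejected in 4% to 5%. A small weight is enough to mislead: at 8% the error rate is already more than three times nominal.

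**Case 2: outcome is change from the second assessment, driving level unrelated to rate of decline.** Subtracting the baseline score removes the driver's stable cognitive level, and with it the link to usual driving. Simulated rejection for the uncentred DBI was 3% to 7%, so the leak is gone.

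**Case 3: as case 2, but driving level related to rate of decline.** With r = 0.3 between usual driving and decline, and the SD of 3-year decline assumed at 0.5 to 1.0 outcome SD, the uncentred DBI rejected in about 11% to 61% of runs and the deviation term in 5% to 6%. The association is real but lies between drivers: it says who will decline, not that the sensors saw a driver change.

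**Do the stated processing steps prevent this?** Rates per trip, turn, intersection or mile leave a driver's usual rate in place. Min-max scaling over all drivers is a linear rescaling and keeps every difference between them. Scaling within each driver would remove most level differences, but the article does not say that this is done.

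**The case against.** The strongest reply is that this rests on silence in a condensed article. A mixed model with time-varying covariates is a broad class that includes the mean-plus-deviation form, and such parameterisation is often left to the full protocol or SAP, which is not shown. The Data processing phase also says that several preliminary models will be assessed. The text speaks repeatedly of changes in cognition, names reliable change indices, and describes within-driver reasoning, all of which lean towards case 2, where stable differences do no harm. Finally, no passage says that a significant LME coefficient will count as detection; the LME is a comparator for the neural network.

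Much of this stands, and it rules out three stronger readings that a reader might infer:

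- **That raw sensor values enter the model.** The features are processed and normalised. What can be said is that they are not stated to be centred on the driver.
- **That the coefficient is merely concurrent and so cannot be an early warning.** No lag is given. Data are downloaded at the quarterly visits, so a 3-month aggregate ending at a visit could well precede the score.
- **That the plan has chosen a wrong model or will report false detection.** That depends on an outcome and a parameterisation that the article leaves open.

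The reply does not remove the point. The article itself names the model, its inputs and the target, and no stated step isolates within-driver change. A change outcome helps only if driving level is unrelated to decline. The Background reports driving patterns that predicted impairment, and Travel patterns describes avoidance as compensation for age-related deficits, so that cannot be taken for granted.

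**Conclusion.** The point holds conditionally. If the LME has one coefficient per DBI and models cognition at each visit, stable differences between drivers can pass for detection of change: about 17% to 96% rejection with no within-driver effect. If it models change from the second assessment, the artefact disappears unless driving level is related to rate of decline; the finding is then between-driver prognosis, at about 11% to 61% rejection under the stated assumptions. A separate within-driver term stays close to nominal in both situations. The DBI intraclass correlations, the between-driver correlations and the spread of decline are assumptions, so the ranges show sensitivity and do not forecast this study's error rate. Scaling within each driver would also reduce the problem.

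**What to change.** In Predictive modeling phase:

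1. State the LME outcome: score at each visit, change from the second assessment, or reliable change index.
2. Enter each DBI as two terms: the driver's own mean (or baseline-quarter value) and the deviation from it in each interval.
3. Rest any LME-based claim of detecting change on the deviation term, and report the driver-mean term as the between-driver result.
4. State that the DBI interval precedes the cognitive visit. This is a clarification, not the correction of an error.

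The cost is one more term per DBI and no new data. The within-driver estimate is less precise than the mixed one: its variance is larger by a factor of 1/(1−w). In the settings above that is 1.09, 1.20 and 1.76 for DBI intraclass correlations of 0.5, 0.7 and 0.9, so standard errors rise by about 4%, 10% and 33%.

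### Features are selected on cognitive change before modelling and the models are then assessed on that same change, with no hold-out described; unless selection is confined to training drivers, the LME's predictive ability will look better than it is

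*Protocol article*

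**What the plan says.** The Protocol article, Data processing phase, describes three steps: preliminary models to explore functional form; feature extraction and scaling; and feature reduction. The purpose of the last is stated: "The third processing step is the reduction of the number of features to prevent overfitting the model". Two selection methods are named and compared. The first is described thus: "Elastic net regression adds a penalty and bias to the models resulting in the retention of only the critical variables". The second is SHAP, a global method that "will be used to compute the feature importance of each variable in predicting cognitive change". Selection is therefore driven by the outcome.

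The next subsection, Predictive modeling phase, opens: "Two different methods will be used to model the prediction of changes in cognitive functioning followed by a sensitivity analysis". For the first of the two methods it states: "This LME method will use the processed data aggregated at weekly, monthly, and 3-month intervals along with the features determined by the SHAP analysis". The RNN is said only to take input features at each time step; the text does not say whether these are the SHAP-selected set. Finally, the driving behavior index (DBI) "algorithms generated will be assessed for ability to predict changes in overall cognitive functioning as well as other specific domains".

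The Results paragraph of the Abstract gives the same order: normalization, external data, critical features, then the comparison of traditional models with the RNN.

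**The concern.** The selection step and the model that follows have the same target. If both use the same drivers, chance associations in that sample decide which features survive. The LME is then fitted and judged on the data that produced those associations. Feature reduction does make a model simpler, but done this way it does not make the performance estimate honest. The data have already been searched, and the final fit does not show how widely.

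This bears on the study's main question. The objective is whether the sensors can detect cognitive change, and the first aim includes finding the sensor components that best predict it. An index built from noise could pass for an early-warning signal, and the components named as best could be those that happened to correlate in this cohort.

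The obvious later addition, cross-validating the final LME, would not cure this if the feature list had already been fixed using every driver. That is why the order of steps matters, and not only the absence of a sentence on validation.

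**Working it through.** **The order as written**

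1. Selection criterion: importance for predicting cognitive change (Data processing phase, third step).
2. Hand-over: the SHAP features go to the LME (Predictive modeling phase).
3. LME target: change in cognitive functioning, the same as in 1.
4. Assessment: ability of the DBI algorithms to predict cognitive change, the same target again.
5. Validation: no split, hold-out, cross-validation, bootstrap correction or external sample appears in the article. The only further check on the models is an unspecified sensitivity analysis.

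**Inputs for the size**

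The article states no accuracy figure, so there is none to reproduce.

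- Drivers: 384 (Sample size calculation; 200 / 0.521 = 383.9), or 460 × (1 − 0.20) = 368 after attrition.
- Share changing: 52.1% (same section).
- Candidate features P: not stated; assumed 20 to 200. Table 4 names about 20 DBIs as open-ended examples.
- Features kept: not stated; assumed 10.
- True signal: none, so an honest AUC is 0.50.

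**Simulation A: binary outcome**, n = 368, independent features ranked by marginal correlation, linear model, 10-fold cross-validation (CV), 200 replicates:

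| P | Apparent AUC | CV after selection | Selection inside folds |
|---|---|---|---|
| 20 | 0.62 | 0.55 | 0.49 |
| 50 | 0.66 | 0.60 | 0.49 |
| 100 | 0.69 | 0.64 | 0.49 |
| 200 | 0.71 | 0.67 | 0.49 |

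A rerun agreed with these values to within 0.01.

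**Simulation B: continuous change score**, n = 384, features ranked by linear SHAP importance, |b_j| × mean|x_j − x̄_j|, top 10 refitted, AUC computed for the top 52.1% of scores, 500 replicates:

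| P | Apparent AUC | CV after selection | Selection inside folds |
|---|---|---|---|
| 10 (no selection) | 0.57 | 0.49 | 0.49 |
| 20 | 0.60 | 0.54 | 0.49 |
| 50 | 0.63 | 0.58 | 0.50 |
| 100 | 0.64 | 0.61 | 0.50 |
| 200 | 0.65 | 0.61 | 0.50 |

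The first row separates two effects. A 10-feature model assessed on its own data reaches 0.57 without any selection, and ordinary cross-validation removes that. What remains in the third column for larger P is due to selection alone, and only repeating selection inside the folds removes it.

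**Simulation C: mixed model**, random intercept, 12 visits, intraclass correlation 0.5, n = 384, features ranked by |t|, top 10 refitted, 200 replicates. For P = 20 to 100, 10% to 53% of the retained terms had p < 0.05, and the overall model test was significant in 48% to 100% of runs. Selecting in one half of the drivers and testing in the other brought these to 4.6% to 5.9% and 5.5% to 8%. The Monte Carlo standard error of a 5% rate over 200 runs is √(0.05 × 0.95 / 200) = 1.5 percentage points. The bias is therefore not peculiar to a cross-sectional model.

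**The case against.** The strongest reply is that the article gives the order of the steps but not which drivers enter each one. Selecting before modelling is compatible with selecting inside training data, and a condensed article may leave fold structure to a fuller plan. That stands as a limit on the conclusion. A reader might infer that features are chosen on the whole dataset; the text neither says so nor excludes it. It does not dispose of the point, because the article fixes selection as a finished processing step whose result is handed on, and offers that step as the overfitting safeguard.

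Other stronger readings also fail:

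- **Both models inherit the bias.** Only the LME is said to take the SHAP features. The supportable statement is that the comparison may be uneven.
- **Reported p-values and AUCs will be wrong.** The article announces neither for these models. AUC is used here as a convenient scale, and the p-value results apply only if such tests are made.
- **Min-max scaling leaks the outcome.** The plan says "data will be normalized using the minmax approach", but this scaling does not use the outcome. A check with 10 noise features scaled on all 368 drivers gave a cross-validated AUC of 0.48, so no optimism.
- **The bias is large whatever the feature count.** With about 20 candidates, the number of examples in Table 4, cross-validation after selection gives 0.54 to 0.55, not the 0.64 seen with 100.

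The comparison of elastic net with SHAP, the sensitivity analysis and the study of DBI accuracy and stability are real checks. Nothing in their description separates selection from assessment.

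**Conclusion.** The point holds conditionally. The article puts outcome-driven selection ahead of an LME that predicts the same outcome, assesses the indices on that prediction, and describes no separation of drivers between selection and assessment. Unless selection is confined to training drivers, the LME's apparent predictive ability will be optimistic even with no signal, and cross-validating only the final model will not correct it.

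Over both outcome types, with no signal, 368 to 384 drivers and 10 features kept, 20 to 200 candidates give an apparent AUC of about 0.60 to 0.71 and about 0.54 to 0.67 with cross-validation after selection. Nested selection gives about 0.50. These figures assume independent noise features and linear models, and the counts of candidate and retained features are assumptions. The direction of the bias is secure; its size in this study cannot be fixed from the document. It should be settled before the models are fitted.

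**What to change.** State in the analysis plan that:

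- data are split by participant, with all visits and trips of a driver in one fold;
- choice of functional form, elastic net and SHAP selection, and tuning are repeated inside each training fold (nested cross-validation), or a participant-level hold-out is locked before the first processing step; scaling constants are also taken from training drivers, for good order;
- the RNN's input features are specified, and LME and RNN use the same folds;
- predictive performance is reported only on held-out drivers;
- any inference on SHAP-selected LME terms is descriptive, and the number of candidate features is reported.

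The cost is analysis code and computing time, with no change to recruitment, visits or instruments. Headline accuracy will probably look less favourable, and a locked hold-out would leave fewer drivers for model building; nested cross-validation avoids that.
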